## Discussion

Over six years of preliminary research [29, 30], an NIDCR-funded planning grant (R34DE023158), and refinement in collaboration with NIDCR (U01DE026739), protocols were developed to minimize recognized large RCT challenges in participant recruitment, enrollment, and retention. Reaching the study’s targeted enrollment is achievable at a pace of 8–9 dyads enrolled weekly over 24 months given that more than 800 age-eligible children visit the recruitment sites each month, at least half of 4–5 year olds and one-quarter of 2–3 year olds in the target population experience ECC, and a preliminary study of 108 families found a 95.6% acceptance rate without financial incentive [30]. While the preliminary study involved only one recruiter 2.5 days/week for five months, this study will engage three CHW recruiters and three support staff five days each week for 24 months and will provide financial incentives. Recruitment and enrollment rates will be monitored weekly and additional resources invested as necessary.

This study encourages retention through financial incentives, user-friendly technology, rapport between CHWs and parents, assistance to families to address social service needs, and an approach that is non-judgmental and encouraging. Initial and semiannual CHW training will help ensure that study protocols are well understood and that appropriate communications and referral skills are established. Adherence to study protocols will be monitored for fidelity by a CHW supervisor and the Study Team through recurrent retraining and bi-weekly meetings that identify and address problems as they arise and weekly review of CHW logs and DCC data for timeliness, completeness, and accuracy (e.g., reported data that are within allowable limits). Corrective action plans will be developed and implemented as needed.

The primary assessment of intervention effects will use an intention-to-treat approach. Implementation data will allow testing of dose–response effects if some subjects do not complete all intervention activities thereby enabling assessment of potential moderating effects attributable to delivery of varying levels of intervention intensity.

Through these efforts, the study team seeks to maximize its ability to meet the study’s *Impact*, *Translational*, and *Exploratory* objectives and build understanding of oral health behavior change that holds promise to improve individual children’s oral health and the oral health of socially disadvantaged populations.

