The fifth Program component—Follow up and Facilitation—will be achieved over six months through at least three CHW-parent interactions and automated delivery of standardized study-specific text messages. Of the three interactions, at least one will be an in-home visit (or, if necessary, a virtual in-home visit) that will include a timed tooth brushing observation during which CHWs will provide additional guidance and instruction if necessary. Two additional interactions may be conducted by telephone or reciprocal text messaging. Interactions will focus on review and reinforcement of the family’s goal and the family’s progress toward fulfilling their self-defined action plan. Up to four additional interactions with parents may be provided by CHWs if needed to address pressing parental concerns related to food, housing, income, employment, or immigration insecurities by making referrals to appropriate community, social service, and legal aid programs. All interactions will be recorded to analyze possible impacts on study outcomes. The standardized text messages are comprised of 4 rounds of 12–13 messages each over the course of the 6-month intervention, with specific hygiene recommendations (*Brush twice a day; Brush your child’s teeth; Use fluoride toothpaste; and Brush for at least one minute*) and dietary/feeding recommendations (*Don’t buy snacks and drinks that cause cavities; Make water your go-to drink; Make eating time, time to eat; Sit to eat, and Don’t snack all day*) based on behavioral intervention targets. Tooth brushing video recordings, obtained at T1 and T2, will be assessed for quality and duration using the Tooth Brushing Observation System (TBOS) protocol developed by Collett, et al. [35].

CHWs will utilize additional MSB App features including instruction on how to conduct each Program component; a library of culturally-, linguistically-, and literacy-appropriate educational materials suitable for distribution to parents by handout, mail or text; and administrative functions for recordkeeping (case management, tracking families’ progress, and maintaining a log of activities) and data transmission to the study’s Data Coordinating Center (DCC).

If the first four components of the MSB Program are not completed at T1, they will be completed at the in-home visit to be scheduled within one week of the CCHPH visit. If not conducted within one week, the CHW will note challenges and reasons for delay in the built-in electronic CHW log.

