**Fig. 2 Fig2:**
[figure not shown]
Study schema. This figure presents an overview of study activities and corresponding timeline. The study schema is organized by timepoint: Baseline (T1); 0–6 Months; and 12 Months (T2) post-randomization. The Baseline (T1) timepoint encompasses recruitment, eligibility criteria, enrollment and randomization procedures, and baseline data collection measures. Baseline study activities include both T1 Intervention and Control conditions. The 0–6 Months timeframe represents follow-up activities of the Intervention group condition. Activities represented under the 12 Month (T2) timepoint include final all follow-up data collection measures and activities for both the Intervention and Control group. Intervention and Control Group study activities are described across all timepoints and differences in conditions delineated by arrows depicting flow of study activities

An overview of data to be collected, data sources, and the time points at which they will be collected is presented in Table 2.

**Table 2 Tab2:** Data collection overview

Type	Source	Subjects	Timepoint
Clinical dental examination data	Dental exam charting form	All children screened	T1
		Intervention and Control Group	T1, T2
Tooth brushing observation data	Video recording and TBOS Checklist	Intervention Group	T1, T2
		Control Group	T2
	Tooth brushing duration documented by CHW	Intervention Group	Home Visit
Interview/survey data	Baseline Survey	Intervention and Control Group	T1
	12-month Follow-up Survey	Intervention and Control Group	T2
	Experience Survey	Intervention Group	T2
MySmileBuddy technology data	MySmileBuddy Program App	Intervention Group	T1, T2
CHW implementation and process data	Screening Phase I Form	All parent/child dyads approached for recruitment	T0
	Contact Information Form	All parent/child dyads recruited for dental examination eligibility screening	T0
	Screening Phase II Form	All parent/child dyads presenting to CCPH for dental examination eligibility screening	T1
	Visit Log	Intervention Group	T1, home visit, throughout Intervention period, T2
		Control Group	T1, T2
	Outreach Failure Log	Intervention and Control Group	Throughout study period

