### Statistical power and data analysis

With power ≥ 80% and 2-tailed alpha = 0.05, a sample size of 300 parent–child dyads per Group is sufficient under various scenarios to detect differences between Control and Intervention Groups (45% vs. 33%, 55% vs. 43%, 65% vs. 53% or 75% vs. 64%) based on a 63.2% one-year caries progression rate among 2–5 year old children treated at the Columbia pediatric dental clinic – a rate consistent with findings from this and other high-risk populations [11, 30, 36, 37]. Accounting for 30% loss to follow up (an estimate higher than experienced in our earlier study), each group will require enrollment of 429 subjects.

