### Comparisons

Logistic regression analysis will compare the odds of having ECC progression between the Intervention and Control Group. The analysis incorporates age and recruitment site to reflect randomization on these variables. If there are any significant Group differences in participant characteristics at baseline, a sensitivity analysis adjusting for potential confounder variables in the regression models will be conducted to help interpret the primary analysis finding. To compare the increase in number of dmft/dfs, we will use a repeated measurements analytic approach.

To model the observed count data, we will use a Poisson mixed model (38, Ch.9) that introduces the number of dmft/dfs and considers these counts to be Poisson distributed conditional upon Gaussian random effects. The model includes indicators for time, Group, recruitment site, age, and Group-by-time. The regression coefficient corresponding to the interaction term is the key parameter of interest for assessing the efficacy of the MSB Program as it represents the post- to pre-treatment ratio of the average rate of dmft/dfs between the Intervention and Control Groups. A random effect is included to account for within-subject correlation and for the possibility of heterogeneity among subjects in the ratio of expected dmft/dfs counts before and after randomization. R packages will be used to fit and carry out inference for the proposed models.

Mediation analysis will be used to test of joint significance of the two paths involving a potential mediator, which was found to achieve the best balance of Type I error and statistical power across the 14 reviewed methods [39]. Potential mediators are risk perception for ECC, self-efficacy for tooth-brushing, skills for tooth brushing, self-efficacy for eating a low cariogenic diet, skills for eating a low cariogenic diet, goal setting reflecting self-regulation processes, physical environmental support, social environmental support, knowledge, positive outcome expectations, and ability to overcome barriers to tooth brushing and adoption of a low-cariogenic diet. This allows for expected partial rather than total mediation, a variable will be declared a mediator if and only if both the test of the regression coefficient of the explanatory factor on the mediator *and* the test of the coefficient of the mediator on the outcome variable are both significant at level alpha = 0.05, two-tailed.

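### The mediator rule and the dose-response plan draw causal conclusions from variables that are not randomised, and as written can declare false mediators and false dose effects

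*Protocol article*

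**What the plan says.** **Mediation.** The second secondary objective is to assess causal pathways, meaning mediators and moderators, from the program to toothpaste use and diet. The Comparisons section lists eleven candidate mediators and fixes the decision: "a variable will be declared a mediator if and only if both the test of the regression coefficient of the explanatory factor". The sentence goes on to require significance, each at two-tailed 0.05, for Group's effect on the mediator and for the mediator's effect on the outcome.

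**Timing and source.** In Table 2 both groups have a baseline survey at T1 and a "12-month Follow-up Survey" at T2, with nothing between. The Data management section draws the motivational and facilitating determinants from these interviews and surveys. App data on diet and fluoride use come from the Intervention Group only. Brushing video is taken at T1 and T2 in the Intervention Group but only at T2 in the Control Group.

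**Dose.** The Discussion says implementation data will allow dose-response testing when some subjects do not complete all activities, "thereby enabling assessment of potential moderating effects attributable to delivery of varying levels of intervention intensity". The Intervention group section adds a second kind of contact: "Up to four additional interactions with parents may be provided by CHWs if needed to address pressing parental concerns" about food, housing, income, employment or immigration. It says all interactions are recorded so that their possible impact on outcomes can be analysed.

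**Primary analysis.** The Discussion states an intention-to-treat approach.

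**The concern.** Randomisation protects the comparison of mediator levels between groups. It does not protect the association between a mediator and a behaviour. Two T2 answers from the same parent can agree for reasons unrelated to the program, such as general engagement, health literacy or a wish to give the expected answer. The rule nevertheless turns that association into a declaration of mediation.

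Delivered intensity has the same weakness. It depends on the family and the community health worker after allocation, and it has no counterpart in the Control Group. A moderator should be a baseline characteristic. The optional contacts are assigned by hardship, which may itself predict caries progression, so any association with outcome is confounded by indication. Completion of planned activities is a different quantity. If engaged families complete more, the bias there would favour the program.

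At stake is the explanatory objective. The Background criticises earlier studies for not analysing mediators or moderators, so readers are likely to take these declarations seriously. The program could be credited with mechanisms it does not have, or support for the neediest families could appear to do harm.

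**Working it through.** **1. The plan's own figure.** "With power ≥ 80% and 2-tailed alpha = 0.05", "a sample size of 300 parent–child dyads per Group is sufficient under various scenarios" ("45% vs. 33%, 55% vs. 43%, 65% vs. 53% or 75% vs. 64"%). The pooled two-proportion formula needs 259, 272, 263 and 274 per group. Power at 300 per group is 85.6%, 83.8%, 85.0% and 83.5%. "Accounting for 30% loss to follow up", 300/0.70 = 429 per group, or 858 in total. The plan's figures are reproduced. It gives no figure for mediation or dose-response.

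**2. False declaration under the mediator rule.**

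Inputs from the protocol: 300 evaluable per group; both paths at two-sided 0.05. Inputs assumed, because the protocol gives none: Group effect on the mediator d = 0 to 0.5 SD; residual mediator-behaviour correlation ρ = 0 to 0.20; true mediator effect on behaviour zero.

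Chance that each path is significant:
- Group to mediator: Φ(d/√(2/300) − 1.96). For d = 0.2, Φ(2.449 − 1.96) = 68.8%. For d = 0.3, Φ(3.674 − 1.96) = 95.7%.
- Mediator to behaviour, by Fisher z with n = 600: Φ(atanh(ρ)·√597 − 1.96). For ρ = 0.10, Φ(2.452 − 1.96) = 68.8%. For ρ = 0.15, Φ(3.693 − 1.96) = 95.8%. For ρ = 0.20, Φ(4.953 − 1.96) = 99.9%.

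The rule needs both, so the joint rate is roughly the product. A simulation of the two regressions, with Group in the second model and 3,000 replicates, agrees:

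| d (SD) | ρ = 0 | ρ = 0.10 | ρ = 0.15 | ρ = 0.20 |
|---|---|---|---|---|
| 0 | 0.3% | 3.5% | 4.4% | 5.1% |
| 0.2 | 3.5% | 47% | 64% | 69% |
| 0.3 | 4.3% | 66% | 91% | 95% |
| 0.5 | 4.6% | 70% | 96% | 99.8% |

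Products for comparison: d = 0.2 gives 47%, 66%, 69%; d = 0.3 gives 66%, 92%, 96%.

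Leaving Group out of the second model hardly changes these rates (at d = 0.3 and ρ = 0.10, 65% against 66%). Adjusting for Group alone is therefore not a cure. The simulation had no direct Group effect on behaviour; where there is one, omitting Group adds a further association that is not sized here.

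**3. Number of tests.** Four candidates are specific to brushing or diet. Pairing those with their own behaviour and the other seven with both gives 4 + 7 × 2 = 18 pairs. If every mediator is moved, none works, and tests are independent at 5%, the chance of at least one false declaration is 1 − 0.95^18 = 60%, with 18 × 0.05 = 0.9 expected. With 11 tests it is 43%. The protocol does not say which pairs will be tested.

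**4. Need-driven contacts.** Logistic regression of progression on 0 to 4 extra contacts within the Intervention arm: 300 children, about 53% progression (one of the plan's scenarios), true contact effect zero, 1,500 replicates. The correlation of need with contacts and the odds ratio of progression per SD of need are assumed:

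| Need-contact correlation | OR per SD of need | Rejection | Spurious OR per contact |
|---|---|---|---|
| 0.3 | 1.5 | 14% | 1.09 |
| 0.3 | 2.0 | 28% | 1.14 |
| 0.5 | 1.5 | 30% | 1.15 |
| 0.5 | 2.0 | 66% | 1.26 |

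Without confounding, rejection is 4% to 5%. Adjusting for need brings it back to about 4% to 6%, provided need is measured and correctly modelled.

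**The case against.** Several points on the other side have force.

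- **The text is hedged.** The Abstract says pathways will be explored, the Data management section calls them putative, and the Discussion ends by naming the objective exploratory. The protocol nowhere claims that these variables are randomised. This stands, but the declaration rule itself carries no hedge.
- **Covariates and multiplicity belong in an analysis plan that is not shown.** For covariates this stands: their absence is no fault, and the remark that partial mediation is expected suggests Group may already be in the second model. For multiplicity it stands only in part, because the stated rule fixes the level at 0.05 for each path.
- **The Discussion sentence is about activities not completed, not the optional contacts.** Correct. A reader might infer that the extra contacts will be counted as dose. The protocol does not say so; it says only that they will be analysed for impact on outcomes. The two analyses have separate biases, probably in opposite directions.
- **Not everything is self-report.** Brushing is video-scored in both groups at T2, and progression is examined by blinded dentists. The shared-report problem therefore falls mainly on survey mediators against reported behaviours. The video helps only partly: it scores quality and duration, not twice-daily use, and the Control Group has no T1 recording.
- **Larger figures are tempting.** A reader might quote 96% to 99.9% false declarations at correlations of 0.15 to 0.20. That is the second path alone; the rule requires both. A full cross-product of 11 mediators and two behaviours would give 22 tests and a 68% chance of at least one error, but no such pairing is stated.
- **A complier average causal effect is not a clean replacement.** It requires that families below a delivery threshold gain nothing. They would still receive text messages, family supplies and T1 instruction.

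**Conclusion.** The concern holds in a limited form. Applied as written, the mediator rule can declare false mediators often, about 47% to 95% of the time, if the program shifts the mediator by 0.2 to 0.3 SD and a residual correlation of 0.10 to 0.20 remains. Those inputs are assumptions. With no residual correlation the rate is about 4%, and if the program does not move the mediator it is at most about 5%. It would therefore be wrong to say that the rule will produce false mediators.

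Calling delivered intensity a moderator with attributable effects is incorrect as stated. The planned analysis of need-driven contacts can make them look harmful; the size and even the net direction of bias across the dose analyses depend on quantities the protocol does not give.

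The primary intention-to-treat comparison and the sample size of 858 are untouched. The point concerns a named secondary objective and should be corrected before analysis.

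**What to change.** 1. In the mediator-to-behaviour model, include Group, the baseline mediator and the baseline behaviour from the T1 survey, which is given in both arms. Survey items are not listed, so confirm that both are asked at T1. This removes only the confounding that the baseline values capture.
2. State which mediator-behaviour pairs will be tested, and apply Holm or false-discovery control across them.
3. Replace the declaration of a mediator with a statement that results are consistent with mediation.
4. Reserve the term moderator for baseline variables.
5. Analyse completion of planned activities separately from need-driven contacts, and report both as associational. Do not require a complier average causal effect.

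Cost: wording and light programming, with no new data if the T1 items exist. Fewer mediators will be declared.

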## Items from world health organization trial registration data set

**Table Taba:**

Data category	Information
Primary registry and trial identifying number	Trial registration was completed through the U.S. National Library of Medicine ClinicalTrials.gov website (Identifier: NCT04845594)
Date of registration in primary registry	4/13/2021
Secondary identifying numbers	Not Applicable
Source(s) of monetary or material support	National Institute of Dental & Craniofacial Research of the National Institutes of Health (U01DE026739)
Primary sponsor	National Institute of Dental & Craniofacial Research of the National Institutes of Health (U01DE026739)
Secondary sponsor(s)	Not Applicable
Contact for public queries	*[name],* PhD, MS, RD, CDN
	Columbia University College of Dental Medicine
Contact for scientific queries	*[name],* PhD, MS, RD, CDN
	Columbia University College of Dental Medicine
Public title	Family-centered Behavioral Intervention to Reduce Early Childhood Caries: The MySmileBuddy Program efficacy trial
Scientific title	Randomized Efficacy Trial of MySmileBuddy, a Family Centered Behavioral Intervention to Reduce Early Childhood Caries
Countries of recruitment	United States
Health condition(s) or problem(s) studied	Early childhood dental caries
Intervention(s)	Intervention: Tooth brushing observation at T1 and during home visit with feedback and instruction immediately following observations; two administrations of the MSB technology (i.e., iPad app) by CHWs at the CCPH site (~ 30 min, face-to-face contact at T1 and T2, with T2 administered for data collection purposes only); six months of automated text messages (4 rounds of messages with approximately 50 messages each regarding key intervention topics: Brush twice a day; Brush your child’s teeth; Use fluoride toothpaste; Brush for at least one minute; Don’t buy snacks and drinks that cause cavities; Make water your go-to drink; Make eating time, time to eat; Sit to eat, don’t snack all day); one in-person, in-home visit and two telephone/text message follow-ups by CHWs; up to 4 additional supportive CHW contacts, in-person or by phone/text message are allowed, as needed, to address urgent social issues and will be recorded to discern potential impact on study outcomes
	Control: Mimic standard of care, providing paper-based educational handout plus toothbrushes and fluoridated toothpaste for the child at T1

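### Intervention intensity received is not randomised and varies only in the Intervention Group, so the Discussion cannot treat it as a moderator or attribute outcome differences to it

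*Protocol article*

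**What the plan says.** The Discussion states "The primary assessment of intervention effects will use an intention-to-treat approach". The next sentence reads "Implementation data will allow testing of dose–response effects if some subjects do not complete all intervention activities" and continues "thereby enabling assessment of potential moderating effects attributable to delivery of varying levels of intervention intensity".

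The Intervention group section describes two kinds of contact:
- **Core contact.** After the T1 session, follow-up "will be achieved over six months through at least three CHW-parent interactions and automated delivery of standardized study-specific text messages".
- **Additional contact.** "Up to four additional interactions with parents may be provided by CHWs if needed to address pressing parental concerns related to food, housing", and likewise for income, employment and immigration insecurity.

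That section then says "All interactions will be recorded to analyze possible impacts on study outcomes". The WHO registration table says of the additional contacts that they "will be recorded to discern potential impact on study outcomes".

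Four other places bear on the point:
- Control group: the only interim contact with community health workers (CHWs) is to schedule the T2 visit.
- Explanatory objective: the factors that may condition the effect are demographic, social and contextual.
- Background: caries is concentrated in minority and socially disadvantaged children.
- Comparisons: the only confounder adjustment described is a sensitivity analysis for baseline differences between Groups.

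**The concern.** The Discussion treats non-completion as an opportunity to learn what intensity does. How much of the program a family receives is decided after randomisation, by circumstances that may themselves predict caries. The additional contacts go to families with social hardship, and the article itself describes the disease as concentrated among the disadvantaged. Completion of the core activities plausibly tracks how engaged a family is.

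Two misreadings could follow. Core contacts could look protective because engaged families do better anyway. Need-triggered contacts could look harmful because the families who receive them start at higher risk. Either could be reported after a null primary result as evidence about intensity.

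**Working it through.** **1. The plan's own figures.** The article gives none for dose-response, so I checked the sample size that supplies n. With the pooled two-proportion formula, two-sided alpha 0.05 and 300 per Group, power is 85.6% (45% vs 33%), 83.8% (55% vs 43%), 85.0% (65% vs 53%) and 83.5% (75% vs 64%). All exceed 80%. Loss to follow-up: 300 / (1 − 0.30) = 428.6, so 429 per Group and 2 × 429 = 858. The stated figures reproduce.

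**2. Can dose be a moderator here?** Let G = 1 for Intervention and 0 for Control, and let D be the amount of program contact received. The moderation model is logit P(progression) = a + bG + cD + d(G × D). Control families receive no program contact, so D = 0 whenever G = 0. Hence G × D = D for every family. The last two columns are identical and c and d cannot be separated. Only a slope within the Intervention Group can be estimated.

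**3. What that slope contains.** Comparing families at dose d with families at dose d′ gives the causal effect of dose plus the difference in underlying risk between the kinds of family found at each dose. Randomisation balances the Groups. It does not balance families across dose levels within one Group.

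**4. Size under assumptions.** I simulated 2,000 Intervention Groups of 300 children per setting, with no effect of any contact. Inputs from the article: n = 300, 63.2% progression (used at average covariate values in set-up A), up to four extra contacts, three planned follow-ups. Assumed: engagement E and need N are standard normal; logit P(progression) = ln(0.632/0.368) − βE + βN; core contacts ~ Binomial(3, expit(1.0 + E)); extra contacts ~ Binomial(4, expit(−1.5 + N)). Progression was regressed on each contact count separately, unadjusted, with a Wald test at 0.05.

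| β (log-odds per SD) | Core: false positives | Core: apparent OR per contact | Extra: false positives | Extra: apparent OR per contact |
|---|---|---|---|---|
| 0 | 5% | 1.00 | 4% | 1.00 |
| 0.2 | 15% | 0.88 | 13% | 1.13 |
| 0.4 | 42% | 0.79 | 45% | 1.26 |
| 0.6 | 74% | 0.70 | 77% | 1.41 |

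A second set-up (B) counted the T1 session, so core contacts ran from 1 to 4. At β = 0.2, 0.3 and 0.5 it gave 14%, 24% and 50% for core contacts (OR 0.88 to 0.76) and 15%, 27% and 56% for extra contacts (OR 1.12 to 1.30). With no confounding it returned 5%. The test holds its level only when engagement and need do not predict caries.

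**The case against.** The strongest reply is that this is one hedged, conditional sentence about a supportive analysis. The article fixes no model, comparator, covariates or alpha for it, and dose-response is not among the objectives or the specified comparisons. Covariate choice and causal method would normally sit in the analysis plan, which is not at hand. That stands: leaving those details out is no fault. The statement of what the analysis can show is in the article, however, and that statement is wrong whichever model is chosen.

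Other parts of the reply also stand, and limit the point:
- A reader might infer that the plan puts the additional contacts into the completion dose. It does not say so. The Discussion speaks of activities not completed, whereas the additional contacts are optional. The concern about them rests on the Intervention group section and the registration table, which plan to relate them to outcomes.
- A reader might infer that completers are known to be more motivated. The article does not say so. Shortfalls may also come from staff or scheduling, and CHWs log reasons for delay.
- A reader might infer that the data can support no dose analysis at all. That is too strong: the T1 interview and survey collect sociodemographic, motivational and facilitating measures, so some adjustment is possible.
- An instrumental-variable estimate per contact, with Group as instrument, may look like the natural repair. Group also assigns text messages and quarterly family-wide supplies, so it does not act only through contacts. With a single binary instrument the estimate is just the Group difference divided by the mean dose difference, which cannot test dose-response.

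**Conclusion.** The point holds as a fault in the stated interpretation. Intensity received is not a moderator of the Group effect in this design, and a within-arm association cannot be attributed to it. For the additional contacts, the article supports confounding by need at both ends: hardship triggers the contact, and disadvantage is linked to caries. For core completion, confounding by engagement is an inference.

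The false-positive range of roughly 15% to 55% rests on an assumed 0.2 to 0.5 log-odds per SD, on the assumed link between these traits and contact, and on an unadjusted regression that the article does not commit to. It illustrates the risk and does not predict this trial's error rate. A reader might take it to threaten the trial's main conclusion. It does not: the primary assessment is by intention to treat, and that analysis and the sample size are untouched. The change is worth making because it governs what the trial may claim about intensity.

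**What to change.** 1. In the Discussion, delete the wording that calls these moderating effects and attributes them to intensity.
2. Define dose for analysis as completed core components: the T1 MSB session plus the three planned follow-ups. Keep need-triggered contacts out of it.
3. Report within-arm dose associations, and all results for need-triggered contacts, as exploratory and descriptive, adjusted for baseline measures from the T1 survey.
4. If a causal estimate for completers is wanted, model completion on baseline data in the Intervention Group to obtain e(X). Then compare completers' progression with the weighted Control rate Σ e(Xᵢ)Yᵢ / Σ e(Xᵢ). Interpret the result as the effect of the whole assigned package (contacts, texts and supplies). State principal ignorability: given X, completing and non-completing families would have had the same expected outcome under Control.
5. Do not use a per-contact instrumental-variable analysis.

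The cost is a wording change and modest extra analysis of data the trial already plans to collect; enrolment is listed as pending, so this can be settled before any outcome is seen. The price of step 4 is wider intervals and an assumption that cannot be tested.
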